# Randomized controlled trial of an 8-week intervention combining self-care and hypnosis for post-treatment cancer patients: study protocol

**DOI:** 10.1186/s12885-018-5046-6

**Published:** 2018-11-15

**Keywords:** Oncology, Group intervention, Hypnosis, Fatigue, Emotional distress

## Abstract

**Background:**

Cancer has a lot of consequences on patients’ quality of life (such as cancer-related fatigue (CRF), sleep difficulties and emotional distress) and on patients’ partners and their relationship, such as distress and communication difficulties. These consequences are undertreated, and interventions based on hypnosis often focus on breast cancer patients only. This paper describes the study protocol of a longitudinal randomized controlled trial aiming to assess the efficacy of an 8-week intervention combining hypnosis and self-care to improve cancer patients’ CRF, sleep and emotional distress and to indirectly improve their partners’ distress.

**Methods:**

A power analysis required a total sample of 88 patients. To test the efficacy of the intervention, results of the experimental group receiving the intervention will be compared to those of the control group. Data will be collected by questionnaires, relaxation tasks, an attentional bias task, and everyday life assessments measured at four different times: 1.) before inclusion in the study (baseline); 2.) after the intervention; and 3.) at 4- and 12-month follow-up. Partners’ symptoms will also be evaluated with questionnaires at the same measurement times.

**Discussion:**

There is a growing interest in alternative approaches (such as hypnosis) in addition to standard therapies in oncology settings. The results of this study should be useful for improving knowledge about long-term efficacy of hypnosis-based group interventions for CRF, sleep and distress among all types of cancer patients and their partners, and to better understand the mechanisms of emotional regulation in cancer patients through the attentional bias task.

**Trial registration:**

ClinicalTrials.gov (NCT03144154). Retrospectively registered on the 1st of May, 2017.

**Electronic supplementary material:**

The online version of this article (10.1186/s12885-018-5046-6) contains supplementary material, which is available to authorized users.

## Background

It is predicted that 40% of the population will be diagnosed with cancer at least once, which has a lot of consequences for them and their relatives [1, 2]. First, a meta-analysis showed that 46–99% of cancer patients experience cancer-related fatigue (CRF) [3], which can be defined as “a distressing persistent, subjective sense of physical, emotional and/or cognitive tiredness related to cancer or cancer treatment that is not proportional to recent activity and interferes with usual functioning” [4]. The burden of CRF is high for patients who must endure social, financial, and functional negative consequences associated with this symptom [3, 5]. Second, a large proportion of cancer patients suffer from emotional distress, defined as “an unpleasant experience of an emotional, psychological, social, or spiritual nature that interferes with the ability to cope with cancer treatment” [6–10]. Emotional distress negatively influences treatment adherence [6] and results [6, 11, 12], and patient’s general quality of life [6, 13]. Fear of cancer recurrence is also linked to emotional distress [14–16]. One explanatory process of this relationship could be the presence of an attentional bias toward threat, which can be defined as selective processing of threatening information; in this case it is referring to cancer-related information [17–20]. Third, cancer also affects patients’ relatives. Partners of cancer patients often become the main caregiver for their ill spouse [21, 22] and can feel distressed [23–25] and tired [26, 27]. Changes in couple’s communication, intimacy, and sharing of responsibilities has also been noted [28–30]. Patients’ emotional distress and CRF in addition to their partners’ burden can persist for years after the end of cancer treatments [5, 31–33].

Despite the prevalence of patients’ emotional distress and CRF, and the impact of cancer on relatives, these consequences are still underdiagnosed and undertreated by healthcare professionals [6, 7, 34]. Some studies have shown the positive impact of psychological interventions on patients’ emotional distress [34–36] and CRF [35–38]. Some alternative methods such as hypnosis-based interventions have also been tested. Hypnosis can be defined as “a procedure during which a health professional or researcher suggests that a patient or subject experience changes in sensations, perceptions, thoughts, or behaviour” [39]. Several studies have demonstrated the positive impact on various sides effects of cancer treatments such as CRF, sleep, and distress of hypnosis taught alone [36, 38, 40–45], or combined with self-care techniques [41, 46, 47]. Most of these studies focus on breast cancer patients. However, other cancers may have different adverse physical and psychological effects. For example, mortality rates vary according to the localisation of the tumour [48]. Additionally, some cancers such as prostate and gynaecological cancer directly impact the patients’ sexuality, because they alter or remove symbols of masculinity or femininity (e.g. erection, libido, fertility…) [49–53], with high impact on couple’s intimacy and communication [29, 54–56]. Another example relates to brain tumours, which can lead to cognitive deficits, aphasia, visual field defects, motor deficits and personality changes [57, 58]. All these adverse effects are specific to the type of cancer and may have specific impact on the psychological adaptation to the disease.

## Objectives

Our primary goal is to assess the efficacy of an 8-week group intervention combining hypnosis and self-care to improve fatigue in all types of cancer patients, after treatments. The secondary goals are to assess the efficacy of this intervention to improve other patients’ well-being-related variables (emotional distress (anxiety and depression), sleep, fear of cancer recurrence, psychological adjustment to the disease, emotional regulation skills, cognitive functioning, and physical activity). As the intervention will address various fields such as communication with relatives, we will also assess its impact on the couple’s dynamic, and on partner’s distress. Finally, the link between the decrease in patients’ distress and a possible attentional bias will be assessed in order to better understand the emotional regulatory mechanisms in cancer patients.

## Methods and design

### Design

Figure 1 illustrates the longitudinal randomized waiting-list controlled trial design used in our study. Ethics approval has been obtained from the Comité d’Ethique Hospitalo-Facultaire Universitaire de Liège. The waiting-list control design allows every participant to benefit from the intervention, which will make it possible to recruit more patients than in a no-treatment control design. It also controls the influence of natural recovery from cancer treatments and spontaneous improvement or deterioration of symptoms [59]. Each intervention will start when 16 patients have successfully completed the screening and the first measurement time (T1). Those patients will be randomized into two groups of eight participants: the first group will receive immediate intervention (intervention group) and; the second group will receive it (at the latest) 4 months later (waiting-list control group).

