#### One-year follow-up (T4)

One year after having participated in the intervention, each patient is contacted by the researcher to schedule a final group session with the therapist in order to evaluate the long-term benefits of the intervention. They discuss the application of learned skills in their daily life, perform one hypnosis exercise, and participants also have to complete some questionnaires (see Table 1). We expect the follow-up participation rate to be high, as most patient really appreciate the group session.

At each measurement point, the risk of missing responses is very low, as patients complete the scales in the presence of the investigator, who check every questionnaire after completion. All data are anonymized. A code is attributed to each participant and used during the whole study. Only the researchers involved in this study have access to the final datasets.

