### Statistical analyses

Baseline (T1) demographic, medical, and psychological data will be compared between groups to test for initial groups equivalency using inferential statistics, including analyses of variance (ANOVA) and chi-square tests. Group-by time changes, and pre- and post-assessment comparison of each variable within each group will be assessed using repeated measures MANOVA, on the participant who completed all the needed assessments times. The link between a decrease in distress and attentional bias will be assessed by correlations. Correlations will also be used to assess the links between the data from the patients and their partners, and we will measure the evolution of the partners using repeated measures MANOVA. All tests will be two-tailed, and the alpha will be set at 0.05. Statistical analyses will be performed after T3 and after T4.

All participants will be informed by e-mail about the final results of the study. Scientific publications will also be planned.

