There are some limitations of our study. The number and length of assessments completed by the participants could lead to some dropouts. It is possible that only motivated and compliant patients will complete all the assessments, which would bias the results of the study. However, it is important to point out that the participants have to complete assessments with at least a 3-month interval between them, which reduces the possible burden experienced by the participants. Another limitation is the fact that our intervention has only been proposed for non-metastatic patients in order to minimize the baseline differences of the sample.

In conclusion, our study will provide the initial insight into the short and long-term effects of an intervention combining hypnosis and self-care on the quality of life of all types of cancer patients in remission, on partners’ well-being, on the quality of the conjugal relationship, and on links between emotional regulation, distress, and attentional bias.

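### Only T1–T2 has an untreated comparator, yet the group-by-time plan and the long-term efficacy claim extend to T3 and T4

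*Protocol article*

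**What the plan says.** All references are to the protocol article.

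- **Design.** "The waiting-list control design allows every participant to benefit from the intervention". On timing, "the second group will receive it (at the latest) 4 months later (waiting-list control group"). The section adds that the waiting list controls for natural recovery after cancer treatment. It then gives the first cohort's dates: immediate group April 2017, waiting-list group July 2017.
- **Abstract, Methods.** Efficacy is tested by comparing the experimental with the control group. Measurements are at baseline, after the intervention, and "3.) at 4- and 12-month follow-up".
- **Measurement points.** Every participant completes T1, T2 and T3.
- **One-year follow-up (T4).** Each patient is contacted one year after taking part in the intervention, for a therapist-led group session. There they "perform one hypnosis exercise, and participants also have to complete some questionnaires".
- **Statistical analyses.** "Group-by time changes, and pre- and post-assessment comparison of each variable within each group" are assessed by repeated measures MANOVA in those who completed the needed assessments. "Statistical analyses will be performed after T3 and after T4".
- **Claims.** The abstract's discussion expects the results to be useful for "improving knowledge about long-term efficacy of hypnosis-based group interventions". The main Discussion promises a long-term assessment of intervention effects, and its conclusion refers to short- and long-term effects.
- **Discussion, limitations.** "participants have to complete assessments with at least a 3-month interval between them". That patients in both arms are treated at the later measurements is not listed as a limitation.

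**The concern.** A waiting list gives a randomized untreated comparator only until the waiting group starts. After that, the arms differ in when they were treated, not in whether they were. The article states the design, the test, the analysis times and the claim, and these do not fit together: nothing limits the experimental-versus-control comparison to T1–T2, and nothing says that T3 and T4 are uncontrolled.

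If T3 or T4 enters the group-by-time test, two errors of reading become likely:

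- A significant interaction may come from T2 alone and be taken as evidence of a lasting effect.
- A null arm difference at T3 or T4 may be taken as loss of effect, although a fully lasting benefit in both arms would produce exactly that.

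Within-arm change from T1 to T3 or T4 does not fill the gap. Patients enter less than a year after completing active treatment (Eligibility), so natural recovery is a live alternative explanation. It is also the reason the Design section gives for having a control group.

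**Working it through.** **1. The plan's own figure.** Inputs from Recruitment and Statistical analyses: two-sample t-test, two-sided alpha 0.05, power 90%, d = 0.7. The noncentral t gives n = 43.87, rounded up to 44 per arm and 88 in total; power at 44 per arm is 0.901. The stated sample size reproduces.

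**2. Timeline, in months from the immediate group's start.** Eight weekly sessions (Intervention) = 56/30.4375 = 1.84 months.

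| Event | Calculation | Month |
|---|---|---|
| Immediate group ends; T2 no earlier | 1.84 | 1.84 |
| Controls start | first cohort 3; latest 4 | 3 to 4 |
| Controls end | 3 + 1.84; 4 + 1.84 | 4.84 to 5.84 |
| T3, using the 3-month minimum after T2 | 1.84 + 3 | 4.84 or later |
| T3, as 4 months after the intervention ends | 1.84 + 4 | 5.84 |

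On the 4.84 reading, controls who started at month 3 have just finished and those who started at month 4 are part-way through. On the 5.84 reading, even the latest starters have finished. Only T3 at 4 months from the start would leave the latest starters untreated. The T2-to-T3 gap would then be at most 4 − 1.84 = 2.16 months, against the stated 3-month minimum, and first-cohort controls would already have started.

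T4 needs no inference, because it is timed from each patient's own intervention.

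**3. What the arm difference measures.** Let r be the share of the 0.7 SD benefit that the immediate arm retains, and f the share that controls have gained by the same wave. The expected arm difference is 0.7 × (r − f).

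- T2, controls not started: r = 1, f = 0, difference 0.7.
- T3, benefit fully lasting, controls finished: r = 1, f = 1, difference 0.
- T3, benefit half faded, controls finished: r = 0.5, f = 1, difference −0.35. The immediate arm looks worse.
- T4, both arms one year past their own intervention: if the course is the same in both, r = f and the difference is 0 whether the benefit has lasted fully or gone.

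**4. Does control catch-up cost the planned test power?** The article does not give the correlation ρ between waves. I assume equal correlations and unit SD, and show a range. For the multivariate group-by-time test with n = 44 per arm and k waves, the noncentrality is λ = (n/2) × S/(1 − ρ). S is the sum of squared deviations of the arm-difference profile from its mean, with F degrees of freedom k − 1 and 88 − k. For a single non-zero difference of 0.7, S = 0.49 × (1 − 1/k).

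| Waves (arm differences) | S | ρ = 0.3 | ρ = 0.5 | ρ = 0.6 |
|---|---|---|---|---|
| T1–T2 (0, 0.7) | 0.245 | 0.783 | 0.901 | 0.952 |
| T1–T3 (0, 0.7, 0) | 0.327 | 0.812 | 0.926 | 0.970 |
| T1–T4 (0, 0.7, 0, 0) | 0.368 | 0.805 | 0.925 | 0.970 |

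Example, T1–T3 at ρ = 0.5: λ = 22 × 0.327/0.5 = 14.4, power 0.926.

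The omnibus test loses no power. With nothing left between the arms at T3 and T4, it is still significant about as often as, or slightly more often than, the T1–T2 test. So a significant result over all waves says nothing about persistence.

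**The case against.** The strongest reply is that the analysis section does not name the waves in the between-arm test. Running analyses after T3 and T4 says when they are done, and the text equally allows a T1–T2 arm contrast with within-group follow-up. Detail of this kind is often left to an analysis plan. This stands in part: the documents do not support saying that the plan definitely tests group-by-time over all waves. But the article itself compares experimental with control across four listed times and attaches efficacy to the long term, so the conflict is in the published text.

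Second, T3 timing is inferred. That is fair, and a zero difference at T3 is an assumption when late-starting controls are only part-way through. On every timing consistent with the 3-month minimum, though, controls have at least started.

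Third, the waiting list is openly described, and the primary objective (fatigue) makes no long-term claim. Both are true, which is why the short-term comparison is not in question.

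A reader might also infer a loss of power. Averaging differences of 0.7 at T2 and 0 at T3 gives 0.35 SD, for which a t-test with 44 per arm has about 37% power. The article plans no such average, and the calculation for the test it does plan shows no loss. Nor does the article say that only those attending the reunion supply T4 data, or that the questionnaires follow the hypnosis exercise; the order is not stated.

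**Conclusion.** The point holds as a problem of interpretation. At T4 there is no untreated comparator, by the article's own definition of T4. At T3, inferred at about 4.8 months or later, controls have at least started and on most readings have finished. Followed as written, the plan cannot support a claim of long-term efficacy: the expected arm difference goes from 0.7 SD at T2 to 0 under a fully lasting benefit, and at T4 it is 0 whether the benefit lasts or not.

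This assumes that both arms respond alike and, for the zero at T3, that controls have completed the intervention. The power comparison also assumes equal correlations of 0.3 to 0.6 and complete data.

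It would go too far to conclude that the trial cannot show efficacy or is underpowered. T1–T2 remains a valid randomized contrast, provided the controls' T2 precedes their start, and the 88-patient calculation is unaffected.

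**What to change.** 1. Name the between-arm difference at T2, adjusted for T1, as the confirmatory efficacy contrast, and state that the controls' T2 is measured before they start the intervention.
2. Keep T3 and T4 outside the between-arm efficacy test. Report them as uncontrolled within-person maintenance, by time since each patient's own intervention. Replace the long-term efficacy wording in the abstract, and the matching statements in the Discussion, with descriptive wording, and list the point among the limitations.
3. Optional: have the T4 questionnaires completed before the reunion's hypnosis exercise, and also seek them from patients who do not attend.

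Items 1 and 2 cost wording only; item 3 needs a small change in how the forms are collected. The real price is that the long-term claim becomes descriptive, which is all the design can support after controls start.

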**Fig. 1 Fig1:**
[figure not shown]
Design of the study

The randomization process will be conducted by the principal investigator. Our clinical experience showed us that breast cancer patients are more likely to participate in such intervention. Despite the fact that we do not aim to compare the efficacy of our intervention between different cancer diagnoses, we will ensure that cancer diagnoses are equally allocated between the two groups (experimental vs control) because we want the same number of breast cancer patients in each of these groups. The researcher will conduct two randomizations: one for the breast cancer patients, and one for the other cancer patients. The draw will be operated through a specialized website (https://www.dcode.fr/tirage-au-sort-nombre-aleatoire) in which the investigator will introduce the codes of the participants and ask the software to divide them into two groups (experimental and control groups). The participants do not know the group in which they are included (experimental vs control) until the end of the first evaluation, when the experimenter tells them (T1). The first intervention group started in April 2017, and the waiting-list control group started in July 2017.

### Eligibility

Inclusion criteria include several parameters:age 18 years or older;fluent in French;no history of psychiatric disorders, such as dementia, psychosis or delirium, which does not allow participation in a group intervention or completion of the evaluations;diagnosis of non-metastatic cancer (all tumour localisations accepted); we did not include metastatic patients in order to minimize baseline differences in the sample, as the changing nature and complexity of metastatic cancers could make it difficult to compare the results with non-metastatic cases [60];all active treatments completed for less than a year (surgery, chemotherapy, and/or radiotherapy), in order to form a group of participants who were recently involved in diagnosis and treatments and so increase the likelihood that the difficulties they are dealing with will be more similar;no relapse at the time of inclusion;difficulties as established by responses of at least 4 out of 10 on 1 of the 6 chosen items of the Edmonton Symptom Evaluation Scale [61]; these include physical fatigue, moral fatigue (we decided to split the original item “fatigue (lack of energy)” into two different items, in order to investigate both physical and psychological sides of fatigue), depression, anxiety, fear of recurrence, or ruminations. This cut-off score was chosen to avoid floor effects [59].

### Recruitment

Participants will be recruited over a 2-year period at the University Hospital of Liège (Belgium). Potentially eligible participants are identified in several ways. First, healthcare professionals working with cancer patients (mostly oncologists, radiotherapists, psychologists, and nurses) are informed of the study and asked to talk about it to their non-metastatic patients who have finished their treatment. Interested patients should directly report to the experimenter or are advised to contact us by phone. Second, flyers and posters are displayed in different strategic areas in the hospital (mostly in oncology, radiotherapy, and algology services’ waiting rooms), which allow other health professionals and patients to be informed about the study and to contact us to participate or to talk about the study. Finally, in collaboration with the social nurse, all eligible patients are directly met after their last radiotherapy session, and are offered to participate in the study. Review of the trial process and difficulties encountered are discussed once a month between the researchers. This permitted to improve our recruitment strategies.

The recruitment started in December 2016 and is ongoing. Sample size has been determined by a power analysis in order to detect a difference in the evolution of data between the two groups. The sample size calculation was based on an independent samples t-test for a difference in mean scores. Alpha was set at 0.05, power at 90% and the standardized effect size at 0.7. The Cohen’s *d* of 0.7 is considered to be a medium to high effect size. Psycho-oncology studies which aim to assess the effect of an intervention on the patients’ quality of life often use effect sizes between 0.6 and 0.8 to calculate the sample size [62, 63]. According to this analysis, 44 patients are required in each group for a total of 88 patients.

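### The 88 patients behind the 90% power are the number that must be analysed, with no reserve for the dropouts that the article foresees and its completers-only analysis removes

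*Protocol article*

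**What the plan says.** The Recruitment section of the protocol article bases the sample size on an independent-samples t-test for a difference in mean scores. Its inputs are: "Alpha was set at 0.05, power at 90% and the standardized effect size at 0.7". Its result is: "According to this analysis, 44 patients are required in each group for a total of 88 patients". The Abstract likewise gives 88 as the total sample required. No allowance for loss is mentioned in either place.

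Three other sections bear on this figure:

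- **Statistical analyses** runs the repeated measures MANOVA only "on the participant who completed all the needed assessments times", and specifies the tests: "All tests will be two-tailed, and the alpha will be set at 0.05".
- **Discussion**, under limitations, says: "The number and length of assessments completed by the participants could lead to some dropouts". It adds that perhaps only motivated and compliant patients will finish everything.
- **Design** starts each intervention once 16 patients have completed screening and T1. It continues: "Those patients will be randomized into two groups of eight participants".

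**The concern.** A sample size from a t-test formula is the number of patients who contribute data to the test. Under a completers-only analysis, each patient who leaves before a needed assessment is subtracted from that number. The article describes such losses as possible and sets the analysis rule that turns them into a smaller sample, but it carries the formula's output forward as the trial's total sample. If 88 is also the number randomised, the quoted 90% holds only with essentially no loss.

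What is at stake is how the result on fatigue, the primary goal, is read. The stated power tells a reader how much weight a null result carries, and here it would be somewhat overstated.

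**Working it through.** **Inputs from the article.** Standardized difference d = 0.7, alpha 0.05 and power 90% (Recruitment); two-sided testing (Statistical analyses); 1:1 allocation in batches of 8 + 8 (Design).

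**Input not in the article.** The dropout rate. I use 5% to 20% as an assumed range.

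**Step 1: reproduce the plan's figure.** With n analysed per group, the t statistic has 2n − 2 degrees of freedom and noncentrality d × √(n/2). Solving for 90% power at two-sided 0.05 gives n = 43.87, rounded up to 44 per group, 88 in total. This matches the article exactly. A one-sided test would need only 36 per group (35.65), so the article's figure is the two-sided one.

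**Step 2: look for a reserve.**

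- n = 44: noncentrality 0.7 × √22 = 3.283, power 90.1%.
- n = 43: noncentrality 0.7 × √21.5 = 3.246, power 89.4%.

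Losing one patient per group takes the power below 90%, so 88 contains no hidden allowance.

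**Step 3: randomise 88 and analyse completers.** The expected number analysed per group is 44 × (1 − loss).

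| Assumed loss | Analysed per group | t-test power |
|---|---|---|
| 0% | 44 | 90.1% |
| 5% | 41.8 | 88.5% |
| 10% | 39.6 | 86.8% |
| 15% | 37.4 | 84.8% |
| 20% | 35.2 | 82.5% |

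**Step 4: compare with the batch size.** 88 / 16 = 5.5, so 88 is not a whole number of batches. The next whole number is six, giving 6 × 16 = 96 patients, 48 per group.

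- No loss: power 92.4%.
- Largest loss that leaves 44 per group: 1 − 88/96 = 8.3%.
- 10% loss: 48 × 0.9 = 43.2 per group, power about 89.5%, just under 90%.

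**The case against.** The strongest reply is that no stated figure is wrong. The article says 88 patients are required, which is what the power calculation shows. It nowhere says that exactly 88 will be randomised or that recruitment stops there, and an enrolment target or replacement rule could sit in a fuller protocol that is not shown. This stands in part: the calculation is correct, and if 88 was always meant as the number analysed, the defect is a missing label. But the Abstract calls 88 the total sample, and the article itself gives the analysis set. A reader of these sections would take 90% as the power of an 88-patient trial.

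The article also sounds optimistic about retention. The One-year follow-up section expects high participation and a very low risk of missing responses, and the Discussion notes that assessments are at least three months apart. The first expectation concerns the T4 session and carries no figure. The second concerns questionnaires checked at attended visits, not withdrawal. The spacing is offered as reducing burden, not as removing dropout. None of these supports zero loss. Equally, the article calls dropout possible and gives no rate, so it would be wrong to say that it predicts a particular loss.

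The powers above are for the t-test used in sizing, while the planned analysis is a repeated measures MANOVA. They therefore show what happens to the article's own power claim, not the power of the final analysis. Analyses are planned after T3 and again after T4, and the rule refers to the assessments needed, so loss at T4 alone need not reduce the T3 analysis.

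A reader might infer from the batches that the design contradicts itself, or that the trial would stop at five batches, that is 80 patients. The text supports neither. Six batches satisfy a requirement of 88, and nothing suggests stopping below it.

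**Conclusion.** The point holds as a matter of labelling and stated power, not of arithmetic. Forty-four per group is correct as the number analysed, and the 90% applies only if essentially all 88 patients complete the needed assessments. If 88 are randomised, the t-test power is about 88.5% at 5% loss, 87% at 10%, 85% at 15% and 82.5% at 20%. The shortfall is under 2 percentage points from the nominal 90% at 5% loss and about 7.5 points at 20%.

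This rests on the article's d = 0.7, two-sided alpha 0.05 and the t-test. It also rests on two assumptions: that 88 is the number randomised, and that the loss is equal in the two groups at the rates shown. The mismatch with batches of 16 is minor and contradicts nothing; it only leaves the actual randomised total unstated. Any bias from analysing completers only is a separate question that a larger sample would not settle.

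**What to change.** In the Recruitment section:

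1. Label 88 (44 per group) as the number to be analysed.
2. State an assumed loss rate and its basis.
3. State the total to be randomised and the power for the expected number of completers. If 88 are randomised, that is about 87% at 10% loss and 82.5% at 20%.
4. Reconcile that total with the batches of 16. If six full batches are run, state 96 randomised: power is 92.4% with no loss, at least 44 per group remain analysed up to about 8% loss, and power is about 89.5% at 10%. If 88 is kept, say how the half batch is formed.

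The change needs no added patients. Its only cost is a stated power slightly less favourable than 90% if 88 remains the number randomised.
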